## Abstract

**Background:**

Cognitive function declines with increasing age and maintaining high cognitive functioning especially at late life remains a challenging question to be addressed. Emerging evidence in the role of mushroom in promoting cognition has been produced from limited observational studies but there is a lack of definitive evidence on both longitudinal relationships from prospective cohort studies and clinical efficacy from clinical trials.

**Objectives:**

To explore the definitive evidence of mushroom on cognitive functions among at-risk middle-aged and young-olds.

**Design:**

The first study is a 10-year cognitive assessment follow-up on an existing cohort, the Diet and Healthy Aging (DaHA), which recruited over 1,000 older adults from the year 2010 to the year 2016. The second is a carefully designed randomized controlled trial (RCT) to assess the role of mushrooms in promoting cognitive functioning among around 600 middle-aged adults and young-olds.

**Participants:**

Participants were selected based on specific inclusion criteria, such as being community-living adults aged 45–74 years with a family history of dementia, APOE ε4 allele, or subjective cognitive decline, while consuming mushrooms no more than once a week and having no dementia, along with the exclusion of individuals with neurological or psychiatric disorders and significant sensory or motor impairments.

**Intervention:**

Participants in the intervention group will consume Pleurotus citrinopileatus mushroom powder daily for 24 months, with compliance monitored using electronic diary apps. The powder contains 7.0 mg/g of ergothioneine (dry weight).

**Measurements:**

Cognitive function including Mini Mental State Examination, Rey Auditory Verbal Learning Test, Symbol Digit Modality test, Clinical Dementia Rating etc. along with mental health and biological markers will be measured at baseline, 1 year, and 2 years after baseline.

## Introduction

1

Cognitive declines can begin in one’s 30s, particularly affecting the ability to process new information and solve problems, though most people become aware of the decline in their 40s(Mitchell et al., 2023; Murman, 2015). Over time, this decline can become severe enough to lead to Mild Cognitive Impairment (MCI) and dementia. The latest nationwide epidemiological survey in Singapore reported a dementia prevalence of 10% among those aged 60 years and above (Subramaniam et al., 2015). This figure is expected to further rise in the coming years given the increasing numbers of the older adults in the population.

Maintaining cognitive function with advancing age is an important and challenging question that requires well-founded research with good translational opportunities. This is particularly important for at-risk populations such as Apolipoprotein E (*APOE*) ε4 allele carriers (Harris, 2024), those with a family history of dementia (Lee et al., 2022), and those at an early stage of cognitive decline, known as Subjective Cognitive Decline (SCD) (Jessen et al., 2014). Without early intervention, these at-risk populations groups are likely to progress to dementia. Prevention should be the focus at population level because current anti-dementia therapies only delay the progression of the disease. For example, the latest approved antibody intravenous (IV) infusion therapy, Lecanemab, only showed a moderately lesser decline in measures of cognition and function than placebo and it was associated with adverse events (van Dyck et al., 2023). Epidemiological studies have reported that higher mushroom consumption is associated with better cognitive performance—across word recall, executive function, and prospective memory—and with lower risk of incident dementia (Cha et al., 2024; Ba et al., 2022; Aoki et al., 2024). Mushrooms contain bioactive compounds such as ergothioneine, which has antioxidant and anti-inflammatory activity and has demonstrated neuroprotective effects in cell and animal models, but human evidence for a definitive neuroprotective effect remains limited. In a recent double-blind, placebo-controlled pilot trial, 14 older adults with MCI received ergothioneine supplementation (25 mg per capsule, thrice weekly) for one year. The intervention was well tolerated, and the ergothioneine group showed modest improvements on the Rey Auditory Verbal Learning Test, as well as stabilization of plasma neurofilament light chain levels—findings that suggest a potential slowing of neuronal damage but require confirmation in larger trials (Yau et al., 2024).

In Singapore, we found that participants who consumed mushrooms >2 portions per week had 47% reduced odds of having MCI (Feng et al., 2019). The association between mushroom consumption and MCI may be mediated by interleukin-6 and hypersensitive C-reactive protein (Chen et al., 2024). Those with higher mushroom consumption were also found to have better cognitive performance as assessed by the Digit Symbol Substitution test (DSST)(Ba et al., 2022; Yan et al., 2023; Nurk et al., 2010), Trail Making Test (TMT)(Yan et al., 2023), block design (Nurk et al., 2010), and the Word Learning test (CERAD-WL)(Ba et al., 2022). In an 18-year prospective study in the UK, mushroom consumers were found to have better cognitive performance than non-consumers across multiple cognitive domains. The relationship was observed to be dose-dependent, with those consuming one or more portions per week showing the highest cognitive score (Cha et al., 2024).

However, observational data do not prove causality, prompting five RCTs (3 weeks–6 months; *n* = 30–436), mostly using ergothioneine-rich Hericium erinaceus (HE), which have yielded mixed results: 3 g/day HE for 16 weeks modestly improved MCI cognition (reversed after a 4-week washout) (Mori et al., 2009), and 1.05 g/day for 49 weeks improved MMSE in AD patients (Saitsu et al., 2019), yet higher doses in healthy adults and a 436-subject, 24-week Australian trial showed no benefit (Zajac et al., 2020). Heterogeneity in species, cultivation, dosing, and duration complicates interpretation and generalization.

Mushrooms contain bioactive compounds such as ergothioneine, which has demonstrated antioxidant and neuroprotective effects in cell and animal models (Cheah and Halliwell, 2021; Tang et al., 2018; Cheah and Halliwell, 2012; Wu et al., 2021; Cheah et al., 2016; Wu et al., 2022; Halliwell and Cheah, 2024). However, human data on ergothioneine’s cognitive benefits remain limited. Accordingly, our trial is designed to explore both clinical outcomes and underlying biological mechanisms—such as changes in plasma ergothioneine levels, inflammatory markers, and DNA methylation profiles—rather than to confirm a definitive neuroprotective effect (Figure. 1).

**Figure 1 fig1:**
[figure not shown]
The multi-faceted capabilities of ergothioneine. Following oral administration, ergothioneine can accumulate in the brain (crossing the BBB) and has been demonstrated to counteract multiple pathologies (e.g., mitochondrial dysfunction, neurotoxin accumulation, neuroinflammation, etc.) associated with dementia and other neurodegenerative disorders.

Due to a lack of definitive evidence of mushroom on both longitudinal relationships from prospective cohort studies and clinical efficacy from clinical trials, we propose two related sub-studies. The first sub-study is a 10-year cognitive assessment follow-up on an existing cohort, the Diet and Healthy Aging (DaHA), which recruited over 1,000 older adults from the year 2010 to the year 2016 (Yu et al., 2020). The long-term follow-up will provide further evidence to strengthen the conclusions from the proposed trial. The second sub-study is a carefully designed randomized controlled trial (RCT) to assess the role of mushrooms in promoting cognitive functioning among middle-aged adults and young-olds. With an adequate sample size and a long intervention period of 24 months, we will provide definitive data on the cognitive benefits of mushroom consumption.

## Research aims and hypothesis

2

In this study, we aim to (1) assess the longitudinal relationship between mushroom consumption and cognitive decline, measured by the absolute change in Mini Mental State Examination (MMSE) scores over a median of 10 years among surviving DaHA participants; (2) test the effects of mushroom powder (two 500 mg capsules per day) on cognitive function measured using the Symbol Digit Modality test (SDMT), the Color Trail Test (CTT) and the Rey Auditory Verbal Learning Test (RAVLT) over 12 months and 24 months, in comparison with controls who consume placebo; (3) examine the underlying protective mechanisms using biomarkers of aging (epigenetic clocks and inflammation) and measuring blood ergothioneine levels; (4) explore epigenome-wide DNA methylation changes following mushroom powder intervention and assess whether such changes correlate with cognitive and biomarker outcomes, without presupposing a beneficial direction. We hypothesized that (1) mushroom consumption will predict slower cognitive decline in a dose-dependent manner over a median 10-year period among DaHA participants; (2) daily mushroom powder consumption over 12 and 24 months will improve cognitive function (processing speed, executive function, memory) among middle-aged and young-old adults; (3) daily mushroom powder consumption will lead to favorable changes in inflammatory marker of aging that correlate with the increase in bioactive compounds from mushrooms; (4) daily mushroom powder consumption will lead to changes in DNA methylation profiles.

## Materials and methods

3

### Observational study

3.1

We will conduct a 10-year follow-up on all survivors from DaHA study. The proposed follow-up will consist of a cognitive assessment session using the MMSE and the Clinical Dementia Rating (CDR) scale. Cognitive decline will be quantified as the absolute difference between baseline and 10-year follow-up MMSE total scores. The average decline rate will be calculated by dividing the change in MMSE total score by the time elapsed between baseline and follow-up in years. Cognitive impairment will be defined by a CDR score of 0.5 or above. We have published widely on aging related topics using data from the DaHA cohort (Feng et al., 2019; Ye et al., 2023; Li et al., 2019; Liu et al., 2021). As DNA methylation and inflammation markers have already been measured in over 600 samples from DaHA participants, further bio-sampling is not required. Details of the cohort can be found in our cohort profile paper (Yu et al., 2020).

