### Methods of analysis

3.5

To test the relationship between mushroom consumption and cognition among cohort participants: A linear regression model will be used to assess how baseline mushroom consumption predicts future cognitive changes. A log-binomial regression model will be used to compare the proportion of incidental cognitive impairment cases in the subgroups defined by mushroom consumption. A sensitivity analysis will be performed using a log-binomial model for repeated measures, including assessments at the 5-year follow-up and controlling for major demographic, medical, and lifestyle factors. Pre-specified subgroup analyses will stratify by baseline cognitive status (MMSE ≥ 27 vs. < 27), sex, and education level (≤ secondary vs. > secondary). Interaction terms will test for differential intervention effects.

*A priori* power calculation was performed using G*Power 3.1. Assuming a small-to-medium effect size of Cohen’s d = 0.30 in 24-month MMSE change, two-tailed *α* = 0.05 and 90% power, 235 subjects per arm are required. Allowing 20% attrition at 24 months (Jacobsen et al., 2021), we plan to enroll 300 per arm.

To test the effects of ET-Rich mushroom powder on cognitive function among RCT participants: A linear regression model will be performed to compare changes in cognitive scores at 24 months between the intervention and control arms. A sensitivity analysis will be performed using a general regression model for repeated measures, including assessments at 12 months and controlling for major demographic, medical and lifestyle factors at baseline.

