### Progress and next step

3.7

We have made significant progress in laying the foundation for our proposed studies. The DaHA study has successfully completed two waves of data collection. Wave 1 (2011–2017) recruited 1,010 community-living older adults aged 60 years and above in Singapore, collecting comprehensive data on lifestyle factors and cognitive function. Wave 2 (2017–2020) followed up with over 600 survivors (aged 62–91), providing valuable longitudinal data through established cognitive assessments. This rich dataset forms the basis for the planned 10-year cognitive assessment follow-up, which aims to further explore the longitudinal relationships between diet, nutrition, and cognitive health.

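### The cohort's named decline measure (absolute MMSE change) and its raw impairment proportion do not account for follow-up that varies by years, and the model's MMSE outcome is not fixed

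*Protocol article*

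**What the plan says.** All references are to the protocol article.

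- **Aim 1 (Section 2)** has decline "measured by the absolute change in Mini Mental State Examination (MMSE) scores over a median of 10 years among surviving DaHA participants".
- **Hypothesis 1 (Section 2)** is that "mushroom consumption will predict slower cognitive decline in a dose-dependent manner over a median 10-year period".
- **Section 3.1** gives two MMSE quantities. The first: "Cognitive decline will be quantified as the absolute difference between baseline and 10-year follow-up MMSE total scores". The second: "The average decline rate will be calculated by dividing the change in MMSE total score by the time elapsed" in years. Impairment is a CDR of 0.5 or above, with no time element.
- **Section 3.5** fits a linear regression of later cognitive change on baseline mushroom consumption and does not say whether the outcome is total or per-year change. A log-binomial model will "compare the proportion of incidental cognitive impairment cases in the subgroups defined by mushroom consumption". A repeated-measures sensitivity analysis adds the visit labelled 5-year and adjusts for demographic, medical and lifestyle factors; elapsed time is not in that list.
- **Recruitment dates** span about six years in both places where they are given. Section 3.7: "Wave 1 (2011–2017) recruited 1,010 community-living older adults aged 60 years and above in Singapore". The Introduction describes a cohort "which recruited over 1,000 older adults from the year 2010 to the year 2016". The Abstract gives the same years as the Introduction.

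**The concern.** The hypothesis concerns speed of decline. The measure that Aim 1 names is an amount of decline, and the impairment comparison is of a cumulative proportion. Amount and speed are interchangeable only when everyone is observed for the same time. The protocol's own dates, its use of a median, and its division by elapsed time all indicate that they are not.

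Two things are at stake. First, the per-year rate is defined but given no role, and the model's outcome is left open between two scales that can give different answers to Aim 1. Second, on the scale that Aim 1 names, and in the impairment comparison, a longer-observed person tends to show more loss at the same underlying rate. That adds variation unrelated to mushrooms. If intake at recruitment drifted over the recruitment years, it would also shift the estimated association.

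**Working it through.** The protocol states no cohort sample size or effect size, so there is no cohort figure to reproduce. Its one calculated sample size, 235 per arm for the trial (d = 0.30, two-sided 5%, 90% power), is reproduced by a two-sample t-test (234.46, rounded up) and does not bear on this point.

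**Step 1: spread of follow-up.** Inputs: a recruitment window of 2010–2016 or 2011–2017, and a median of 10 years. Assumptions: even recruitment and one short assessment wave.
- Window midpoint 2013 or 2014, plus 10 years, puts the wave at 2023 or 2024.
- Shortest follow-up: 2023 − 2016 = 2024 − 2017 = 7 years.
- Longest follow-up: 2023 − 2010 = 2024 − 2011 = 13 years. Ratio 13/7 = 1.86.
- If the wave fell in 2025 instead (Section 3.2 projects ages to that year, but for trial screening), the range would be 9–15 or 8–14 years.

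The earlier wave shows the same feature. Section 3.7 dates Wave 2 to 2017–2020. By calendar years, a 2011 recruit was seen at 2017 − 2011 = 6 years or later, and a 2017 recruit at 2020 − 2017 = 3 years or earlier.

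**Step 2: one rate, different lengths of observation.** Total change = rate × years. The rates are assumed.

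| Rate (points/year) | 7 years | 13 years |
|---|---|---|
| 0.1 | 0.7 | 1.3 |
| 0.2 | 1.4 | 2.6 |
| 0.3 | 2.1 | 3.9 |

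Cumulative impairment = 1 − exp(−hazard × years). The hazards are assumed.

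| Hazard per year | 7 years | 13 years | Ratio |
|---|---|---|---|
| 2% | 13.1% | 22.9% | 1.75 |
| 3% | 18.9% | 32.3% | 1.70 |
| 5% | 29.5% | 47.8% | 1.62 |

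**Step 3: follow-up unrelated to intake.** Simulation with no true intake effect: follow-up uniform on 7–13 years, linear decline with mean 0.2 points/year (between-person SD 0.15), error SD 1.5. The intake groups do not differ in total change (difference −0.001) and the impairment risk ratio is 0.999. Total change correlates 0.16 with follow-up length, so elapsed time accounts for about 0.16² = 2.6% of its variance. The per-year rate has a correlation of about 0.

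**Step 4: follow-up related to intake.** Suppose the mean follow-up of the two intake groups differs by 1 year, still with no true effect.
- Total change: 1 × 0.1, 0.2 or 0.3 = 0.1, 0.2 or 0.3 points. The simulation at 0.2 points/year gave 0.202.
- Impairment at 3% per year, 9.5 against 10.5 years: (1 − exp(−0.285)) / (1 − exp(−0.315)) = 0.248/0.270 = 0.92. With the longer-followed group in the numerator, the simulation gave 1.09, which is the same result inverted.
- Per-year rate: simulated difference 0.0002 points/year, effectively zero.

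The sign depends on which group was followed longer.

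**The case against.** **The two measures do not conflict in themselves.** An absolute change and an annual rate can both be reported, and defining the rate shows that the authors knew follow-up varies. This stands. The gap is that the aim names the absolute measure, the hypothesis is about speed, and the analysis section does not say which quantity it models.

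**A journal article need not list covariates.** Section 3.5 lists none for the main cohort models, not even age, and an analysis plan may add elapsed time. This stands as far as the mere absence of a covariate goes. It does not remove what the text fixes: absolute change as the Aim 1 measure and a proportion as the impairment comparison.

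**Time is partly handled elsewhere.** The sensitivity analysis uses the 5-year visit, and the Discussion puts visit number into the longitudinal models. But visit number is there for practice effects, and neither visit number nor a nominal label measures actual years.

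**Visits may be timed to anniversaries.** That would shrink the spread, and visit dates are not given. Dividing by elapsed time would then be nearly redundant, however, and the word median suggests real variation.

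**A reader might infer that the mushroom association will be biased, or its false-positive rate inflated.** The document does not support that. Bias needs intake to be related to recruitment date, and nothing in the text suggests such a drift. A 1-year difference is also not small: with even recruitment over six years and two equal groups, complete separation by date gives only 3 years.

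**A reader might also infer that longer-followed people are counted as faster decliners.** On absolute change they show larger, not faster, decline, and the per-year rate removes the artefact if decline is linear. With a fixed practice or regression-to-the-mean component c, total change is rate × t − c, so the annualised value is rate − c/t and still depends on t. The rate is therefore not a complete cure.

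**Conclusion.** The point holds for the cohort sub-study. The named decline measure and the raw impairment proportion combine rate of decline with length of observation, and the outcome of the main MMSE model is not fixed.

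The likely effect is modest extra noise, about 2.6% of the variance of total change under the Step 3 assumptions. Bias is conditional on a link between intake and recruitment date that the document neither shows nor excludes. Per year of difference in mean follow-up it would be about 0.1 to 0.3 MMSE points and a null risk ratio of about 0.92 (or 1.09 in the other direction).

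These figures rest on assumed declines of 0.1–0.3 points per year, an assumed 3% annual hazard, the stated 10-year median and one short assessment wave. The trial's fixed 24-month endpoint and its sample size are not touched.

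**What to change.** - **Sections 2, 3.1 and 3.5:** name one Aim 1 outcome and use it throughout. Preferably this is MMSE change with each participant's actual years from baseline to assessment in the regression. The alternative is the per-year rate already defined in Section 3.1. Absolute change can still be reported alongside.
- **Section 3.5, impairment:** add elapsed time to the log-binomial models, main and repeated-measures, for example as log years.
- **Both:** compute time from actual visit dates, not from the nominal 5- and 10-year labels.

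The cost is a wording change and one covariate. The dates are needed anyway, because Section 3.1 already plans on "dividing the change in MMSE total score by the time elapsed between baseline and follow-up in years". If the per-year rate is chosen, it is noisier at short follow-up and assumes roughly linear decline, which is why elapsed time as a covariate is preferred.

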### Randomized controlled trial

3.2

We will conduct a randomized, controlled trial to assess the effects of mushroom powders on cognitive function and epigenetic and inflammatory markers of aging. There will be a total of 600 participants: 300 in the mushroom powder intervention arm and 300 in the placebo control arm. An interim assessment will be conducted when the sample size reaches 200 participants. Trial participants will be screened from two community-based observational cohort studies in Singapore [the DaHA (Chan et al., 2018) study and the Aging in a Community Environment Study (ACES) (Liew et al., 2018)], one completed RCT [the Choral Singing RCT (CSRCT)], and open recruitment via newspaper and poster advertisement at community centers, as well as advertisement on social media and websites. The above three studies led by the applicant have successfully recruited and assessed over 1,500 subjects. The mean age of DaHA, ACES and CSRCT participants in 2025 are projected to be 78, 80 and 79 years, respectively. Given the 20.7-year life expectancy at age 65 in Singapore. We estimate that at least 83% of them would be alive when the trial starts. All subjects have had comprehensive cognitive assessment and most of them have consented to be contacted for future research. Once eligible subjects from the two cohort studies are enrolled in the proposed RCT, they will no longer be considered part of the observational cohorts. No further follow-up visits will be conducted on these participants according to the DaHA-ACES cohort protocol, ensuring that the validity of findings from the cohort studies is not affected. This will be clearly communicated to trial participants selected from the cohorts. Our inclusion criteria are: (1) Community-living adult aged 45 years to 74 years. (2) Family history of Alzheimer’s disease or other types of dementia or carrying at least one *APOE* ε4 allele or having subjective cognitive (SCD) defined as “self-reported memory problems that have been getting worse over the past year.” (3) Consume mushrooms no more than once a week. (4) No dementia: CDR global score equal to zero. Exclusion criteria are: (1) Any diagnosis of neurological diseases (e.g., epilepsy, stroke) made by a clinician. (2) Any diagnosis of psychiatric illnesses (e.g., depressive disorders) made by a clinician. (3) Marked hearing impairment, visual impairment or upper limbs motor difficulties that make the person unable to complete cognitive assessment.

Details of the trial’s measurements and procedures will be explained to eligible participants in their native language. Written informed consent will be obtained only after potential participants are satisfied with their understanding of the trial.

